**[contact]**

E-mail: [[contact]](mailto:[contact])

[[contact]]([contact])

All the information requested on the SAE Form should be provided as available. The SAE form must be filled out and signed by the Investigator. All of those events must also be recorded in the appropriate CRF page(s).

The following details should at least be available:

- Patient initials and number
- Patient: date of birth, sex, ethical origin
- The suspected investigational medical product (IMP)
- The adverse event assessed as serious
- Short description of the event and outcome

If applicable, the initial report should be followed by the Follow up report, indicating the outcome of the SAE.

The Safety Department will review all incoming SAE reports for accuracy and completeness. SAEs will be reported to the appropriate authorities and Ethics Committees according to country-specific regulations i.e. summarized at regular intervals of at least one year.

### 10.5.2 Reporting procedures for SUSARs

It must be remembered that the regulatory authorities, and in case of SUSARs which could possibly concern the safety of the study participants, also the Institutional Review Board / Independent Ethics Committee (IRB / IEC) are to be informed. Such reports shall be made by the study management and the following details should be at least available:

- Patient initials and number
- Patient: date of birth, sex, ethical origin
- Name of investigator and investigating site
- Period of administration
- The suspected investigational medical product (IMP)
- The adverse event assessed as serious and unexpected, and for which there is a reasonable suspected causal relationship to the IMP
- Concomitant disease and medication
- Short description of the event:
  - Description
  - Onset and if applicable, end
  - Therapeutic intervention
  - Causal relationship
  - Hospitalization or prolongation of hospitalization
  - Death, life-threatening, persistent or significant disability or incapacity

Electronic reporting should be the expected method for reporting of SUSARs to the competent authority. In that case, the format and content as defined by Guidance (28) should be adhered to. The latest version of MedDRA should be applied. Lower level terms (LLT) should be used.

### 10.5.3 Annual Safety Report

The Annual Safety Report will be provided by the sponsor at least once a year.

This report will also be presented annually to the Independent Ethics Committee (IEC) and to the competent authorities.

#### **10.5.4 Safety Monitoring Board**

A Safety Monitoring Board will be installed for the case of safety concerns and the need of decisions regarding the study progress made by the Sponsor.

## **11. FOLLOW-UP**

### **11.1 Follow-up of study participants including follow-up of adverse events**

A follow-up/ end of study interview will be performed on day 28 (+7), about 21 days after end of treatment.

Follow-up of all SAEs will be done until the event is resolved or the event or sequel is stabilized.

Any medical-related issues or questions requiring immediate resolution or action should be directed to the Medical Supervisor.

### **11.2 Treatment after end of study**

No special treatment after the end of the study is required.

## **12. STATISTICAL METHODOLOGY AND ANALYSIS**

All data analyses will be performed by Bioconsult GmbH, Breitenfurt, after the study is completed and the database is released for unblinding. Statistical programming and analyses will be performed using SAS® Version 9.2 and SPSS® Version 19.

The statistical analyses described in this section will be performed as further outlined in the Statistical Analysis Plan (SAP), which will be finalized prior to unblinding of the database. All data will be listed by treatment group for subjects in the enrolled population, unless otherwise specified.

Continuous data will be summarized by treatment group using the following descriptive statistics: number, mean, standard deviation (SD), minimum, lower quartile (if appropriate), median, upper quartile (if appropriate) and maximum. Categorical data will be summarized by treatment group as the number and percentage of subjects in each category.

## 12.1 Analysis sets

Two different analysis sets are defined

- (Modified) Intention to treat set (ITT)

This analysis set includes subjects who were randomized (and received at least one dose study drug).

- Per-protocol set (PP)

This analysis set comprises all subjects who received study drug (at least one dose) and did not violate the protocol in a way that might affect the evaluation of the effect of the study drug(s) on the primary objective, i.e., without major protocol violations.

After data base close and before unblinding, an “unblinding session” will be held to define the study populations.

## 12.2 Sample size considerations

This study is intended to show the superiority of AP301 vs. Placebo, using “EVLW” (AUC between Day 0 and day 7) as Primary Efficacy Variable.

A mean difference of at least 40% between the two application conditions (AP301 vs. Placebo) will be supposed for EVLW (baseline SD about 40 %), indicating statistically significant reduction of EVLW by use of AP301 compared to Placebo.

A sample size of 40 (20 / group) will be sufficient to show a statistically significant difference between Verum and Placebo with  $p < 0.05$  (two sided) and a power of 80%.

## 12.3 Relevant protocol deviations

There are to be no deviations from this protocol. Any subject whose treatment deviates from the protocol or who is not qualified for the study, may be ineligible for analysis and may compromise the study. Subjects not enrolled in the study cannot receive study drug.

The Investigator and research team must comply with all applicable national and local laws. All protocol deviations will be listed in the study report.

## 12.4 Statistical analysis plan

The statistical analyses described in this section will be performed as further outlined in the Statistical Analysis Plan (SAP), which will be finalised prior to unblinding of the database.

## 12.5 Missing, unused and spurious data

A sample size of 20 evaluable patients / group will be achieved. If applicable, drop-outs will be included in the sample size by using the Last Observation Carried Forward-method with respect to the primary efficacy variable "EVWL". If a patient cannot be included, he/she will be replaced by using the next free number of the respective stratum list.

## 12.6 Endpoints analysis

All efficacy data will be listed by treatment group and subject for the full analysis population. Subjects in the PP population will be identified with an asterisk.

### 12.6.1 Primary endpoint analysis

The primary efficacy variable will be summarised for subjects in both the full analysis and PP population. The full analysis will be the primary analysis population. All other efficacy variables will be summarised for subjects in the full analysis population only.

The primary efficacy variable will be EVWL (measured with PiCCO® technique) between day 0 and day 7 of treatment.

The hypothesis to be tested is superiority regarding the change of the primary efficacy variable "EVWL" in the "AP301 group" in comparison to the "Placebo group".

The null hypothesis is defined as

$H_0$ : Mean EVWL (AUC between Day 0 and Day 7) in the AP301 group = Mean EVWL (AUC between Day 0 and Day 7) in the Placebo group.

The alternative hypothesis is defined formal as

$H_1$ : Mean EVWL (AUC between Day 0 and Day 7) in the AP301 group < Mean EVWL (AUC between Day 0 and Day 7) in the Placebo group.

Statistical tests will be two-tailed at the 5% significance level (Power=80%). The primary efficacy variable (EVWL) will be analyzed confirmatory between the two conditions (AP301 vs. Placebo) using an ANCOVA (analysis of covariance) model or the non parametric Mann-Whitney U-test, dependant on the distribution of data.

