## **7. STUDY OBJECTIVES**

### **7.1 Primary Objective**

To assess the effect of orally inhaled AP301 on alveolar liquid clearance in ALI patients with the purpose to assess the treatment associated changes of extravascular lung water (EVLW) within 7 days of treatment.

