**Day 1:**

The first administration will be performed as soon as possible, depending on the patient's transfer to the ICU, if the interval to the next timepoint for inhalation is more than 8 hours. If the following administration of IMP is planned in less than 8 hours, the IMP should be given at the normal timepoint (08.00 a.m. / 08.00 p.m.).

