### 9.5.2 Screening investigation (Day 0)

Written informed consent must be obtained prior to embarking into any study related procedures. For patients that are temporarily unable to consent (e.g. comatose patients) a subsequent informed consent has to be provided.

The screening investigation aims to screen patients for potential participation. Inclusion and exclusion criteria will be checked.

Demographic data (age, ethnicity, height, weight and gender), vital signs (pulse rate, respiratory rate and temperature), the medical history (including the Glasgow Coma Scale) as well as concomitant medication will be documented. A blood sample for the evaluation of blood gases, clinical chemistry and hematology will be taken. The following scores will be obtained: GOCA (Artigas, et al., 1998), SOFA (Vincent, et al., 1996) and the lung injury score (Murray, Matthay, Luce, & Flick, 1988). The EVLW will be measured via PiCCO® technique. Hemodynamic parameters (HR, systolic BP, MAP, CI, PBV, 24 hours fluid balance and cardiac output) will be analyzed. For women with childbearing potential, a pregnancy test will be performed. Furthermore, the oxygenation index ( $\text{PaO}_2/\text{FiO}_2$ ), the ventilatory plateau pressure and ventilation parameters ( $V_t$ , PEEP, PIP, respiratory rate,  $\text{FiO}_2$ , mean airway pressure and peak airway pressure) will be obtained.

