### 9.5.3 Treatment Phase (Day 1 to 7)

Randomization will be performed prior to first administration of study medication.

All of the following parameters will be measured once in 24 hours, EVLW values will be assessed every 12 hours (between 60 and 120 minutes after administration of IMP) until day 7.

Vital signs will be measured (pulse rate and respiratory rate). A blood sample for the evaluation of blood gases, clinical chemistry and hematology will be taken. The lung injury score (Murray, Matthay, Luce, & Flick, 1988) will be obtained. The EVLW will be measured via PiCCO® technique. Hemodynamic parameters will be analyzed. Adverse events and the concomitant medication will be recorded. Furthermore, the oxygenation index, the ventilatory plateau pressure and ventilation parameters will be obtained.

In case that a patient will be extubated during the treatment phase, no more study medication will be administered. If the patient is reintubated within 48 hours after extubation, study medication will be administered again (until day 7). Nonetheless, all parameters that still will be measured after extubation will be documented.

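### The primary EVLW area starts at the screening visit, before randomisation and the first dose, and section 12.6.1 describes the same variable in three ways that do not agree

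*Protocol*

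**What the plan says.** Protocol section 12.6.1 defines the variable in three ways:

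- As a period: "The primary efficacy variable will be EVWL (measured with PiCCO® technique) between day 0 and day 7 of treatment".
- As a change: "The hypothesis to be tested is superiority regarding the change of the primary efficacy variable".
- As an area, in both hypotheses: "Mean EVWL (AUC between Day 0 and Day 7) in the AP301 group", compared with the placebo group. Section 12.2 and the synopsis also use the Day 0 to Day 7 area.

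Section 7.1 sets the objective: "to assess the treatment associated changes of extravascular lung water (EVLW) within 7 days of treatment".

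The schedule fixes what Day 0 means. Section 9.5.2 and Table 1 make it the screening visit, with one EVLW measurement. Section 9.5.3 covers treatment on Days 1 to 7 and states: "Randomization will be performed prior to first administration of study medication". Table 1 also puts randomisation on Day 1.

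Under section 9.1.5 (Day 1), the first inhalation is given as soon as possible "if the interval to the next timepoint for inhalation is more than 8 hours"; if the next slot is less than 8 hours away, dosing waits for it. After that, EVLW is read every 12 hours, 60 to 120 minutes after inhalation. The planned test is ANCOVA, with no covariate named, or a Mann-Whitney U-test, depending on the distribution of the data.

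**The concern.** An area that opens at screening counts time when no patient has been randomised or treated. Over that stretch the arms can differ only by chance, so it pulls the average difference towards zero. Its length depends on when the patient is screened and on the Day 1 waiting rule, so it adds variation unrelated to treatment.

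The three descriptions in 12.6.1 are not the same quantity. A raw area is not a change, and the schedule has no Day 0 of treatment. This is the trial's only confirmatory variable, and its definition should match the objective in 7.1. At stake are some power and a reported effect that slightly understates the on-treatment difference.

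**Working it through.** **Inputs.** Section 12.2: difference 40%, SD 40% (labelled a baseline SD), two-sided 5%, power 80%, 20 per group. Schedule: EVLW every 12 h, about 1.5 h after each dose (midpoint of 60 to 120 minutes). The time from screening to first dose is not stated, so it is varied as an assumption.

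**1. The plan's own figure.** n per group = 2 × (1.960 + 0.842)² × (40/40)² = 15.7, so 16; by the t distribution, 17. At 20 per group the t-test power is 86.9%. The stated 20 and 80% are not reproduced exactly, but 20 is conservative and does not affect this point. The starting value below is 86.9%.

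**2. Simple dilution.** Take a window of 7 × 24 = 168 h, of which h hours are untreated. Observed difference = 40% × (1 − h/168). Unadjusted t-test, 20 per group:

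| h (assumed) | Untreated share | Difference | Power |
|---|---|---|---|
| 0 | 0% | 40.0% | 86.9% |
| 8 | 4.8% | 38.1% | 83.5% |
| 12 | 7.1% | 37.1% | 81.6% |
| 24 | 14.3% | 34.3% | 75.2% |

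**3. Trapezoids at the scheduled times.** Place one Day 0 reading g hours before the first dose, then 14 readings every 12 h starting 1.5 h after it. The last reading is 13 × 12 + 1.5 = 157.5 h after the first dose. For an immediate, constant effect, the retained fraction is [(g + 1.5)/2 + 156] / (g + 157.5). At g = 8 h this is 160.75/165.5 = 0.971. The table also shows an effect that builds linearly.

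| g (assumed) | Constant effect: difference, power | Linear build-up: difference, power |
|---|---|---|
| 8 h | 38.9%, 84.9% | 37.7%, 82.8% |
| 12 h | 38.4%, 84.1% | 36.8%, 81.0% |
| 24 h | 37.2%, 81.7% | 34.4%, 75.6% |

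**4. Effect of the analysis method.** Simulation with an assumed baseline-to-post correlation of 0.7, a gap uniform on 4 to 24 h, and 13 or 14 post-dose readings per patient, compared with a post-dose area of fixed length:

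- Unadjusted: 84.4% against 87.0%.
- ANCOVA on baseline: 98.7% against 98.8%.
- Mann-Whitney (separate simulation, same correlation and gap range): 82.9% against 85.6%.
- Varying the number of readings alone, unadjusted: 85.8% against 87.0%.

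**The case against.** A pre-dose value is a conventional anchor for an area, and here the screening reading is the only scheduled one, because every treatment-day reading follows an inhalation. An area starting exactly at the first inhalation would have no scheduled reading at its left edge. This stands, and the fix has to respect it.

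The lead-in precedes randomisation, so it is balanced in expectation and cannot favour an arm. This also stands. If baseline is the ANCOVA covariate, almost no power is lost, and on a common time scale the treatment contrast is the same for a level as for a change. That holds only on that route: the protocol names no covariate and allows Mann-Whitney, where about 3 points are lost.

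The limits and scaling of an area can often be left to the SAP. But the protocol itself fixes Day 0 as the start and itself gives the three conflicting descriptions. Also, section 9.5.1 asks only for the date of each measurement, while 9.1.5 asks for the actual timing of each inhalation. If clock times of the EVLW readings are not collected, a later SAP would have to use nominal times.

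A reader might go further and infer that the window ends at a calendar boundary, that patients therefore receive 13 or 14 doses depending on arrival, and that the area is not divided by time. The documents do not establish this. EVLW is read until day 7, but dosing is described as lasting a total of 7 days, so a full seven days is equally supported. No passage says the area is left unscaled.

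**Conclusion.** The point holds as a defect of definition with a modest cost. The area in the hypotheses starts before randomisation and treatment, by a margin that varies between patients, and 12.6.1 does not agree with itself or with 7.1.

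The consequence is dilution, not bias. On the simple formula, unadjusted power falls from 87% to about 84% at 8 h and 82% at 12 h, so the planned 80% is kept. It falls below 80% only with a gap near 24 h, under simple dilution or a slowly building effect. No passage supports a gap that long; the only wait the protocol states is under 8 h, and that is a Day 1 wait, not the whole time from screening. With ANCOVA on baseline the power loss is negligible, although the area difference itself would still understate the on-treatment difference.

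These sizes rest on the protocol's 40% and 40%, assumed gaps and, for the ANCOVA and Mann-Whitney results, an assumed correlation of 0.7.

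**What to change.** Define the primary variable as the time-averaged EVLW: the area over the scheduled post-dose readings, from the first post-dose reading to the last one of the treatment phase, divided by the time elapsed between them. Use the Day 0 screening value as the baseline covariate and not as part of the area. Record the clock time of each EVLW reading.

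Use this one definition in section 12.2, in the hypotheses and text of 12.6.1, and in the synopsis. Remove the mixture of area, change and day 0 of treatment, and state where the window ends.

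The cost is wording changes and one extra time field per reading. No additional measurement or patient is needed. The averaged period opens 60 to 120 minutes after the first inhalation, which is small against seven days.

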|  | 
80%). The primary efficacy variable (EVWL) will be analyzed confirmatory between the two conditions (AP301 vs. Placebo) using an ANCOVA (analysis of covariance) model or the non parametric Mann-Whitney U-test, dependant on the distribution of data.
 
Null and alternative hypotheses:
 H0: Mean EVWL (AUC between Day 0 and Day 7) in the AP301 group = Mean EVWL (AUC between Day 0 and Day 7) in the Placebo group
 
H1: Mean EVWL (AUC between Day 0 and Day 7) in the AP301 group < Mean EVWL (AUC between Day 0 and Day 7) in the Placebo group
 
Secondary Endpoints
 Secondary efficacy variables and exploratory variables will be presented using appropriate descriptive methods, and will be analysed in an explorative sense. Statistical tests and the p-values attached to them will be regarded as descriptive and not as tests of hypotheses.
 
Sample size calculation
 This study is intended to show the superiority of AP301 vs. Placebo, using "EVLW" (AUC between Day 0 and day 7) as Primary Efficacy Variable.
 A mean difference of at least 40% between the two treatment conditions (AP301 vs. Placebo) will be supposed for EVLW (baseline SD about 40 %), indicating statistically significant reduction of EVLW by use of AP301 compared to Placebo.
 A sample size of 40 (20 / group) will be sufficient to show a statistically significant difference between Verum and Placebo with <math>p < 0.05</math> (two sided) and a power of 80%.
 |

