### **9.2 Randomization and stratification**

Subjects will be stratified regarding SOFA-Score (Sepsis-related Organ Failure Assessment) (Vincent, et al., 1996). Cut-off will be made at SOFA scores > 10. Therefore, there will be 2 subgroups (SOFA score ≤ 10, SOFA score ≥ 11). The GOCA score (Artigas, et al., 1998) will be assessed too, to be able to determine different causes of ALI.

Each subject will be randomised to one of 2 groups according to a randomization schedule prepared under the control of Bioconsult GmbH.

A stratified Randomization (strata: SOFA score ≤ 10, SOFA score ≥ 11) will be performed. Treatment allocation will be done using random permuted blocks within strata.

Randomization data will be kept strictly confidential, accessible only to authorised persons, until the time of unblinding. Authorised persons are:

- IT manager of Bioconsult GmbH,
- Drug packaging contractor.

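### The protocol fixes no single confirmatory test: it chooses between ANCOVA and an unadjusted Mann-Whitney test by the distribution of the data, and the fallback does not test the stated hypothesis

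*Protocol*

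**What the plan says.** Protocol section 12.6.1 gives the primary analysis confirmatory status: "The primary efficacy variable (EVWL) will be analyzed confirmatory between the two conditions (AP301 vs. Placebo". It then names two methods for it, "using an ANCOVA (analysis of covariance) model or the non parametric Mann-Whitney U-test, dependant on the distribution of data". The synopsis repeats this: "model or the non parametric Mann-Whitney U-test, dependant on the distribution of data". Neither place says which variable is to be inspected (raw AUC, change or residuals), by what criterion, or when.

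The hypothesis is about means of AUC. The null, "Mean EVWL (AUC between Day 0 and Day 7) in the AP301 group = Mean EVWL (AUC between Day 0 and Day 7", equates the two arms on that mean. The sentence introducing it speaks of change: "The hypothesis to be tested is superiority regarding the change of the primary efficacy variable". On error rates the section says "Statistical tests will be two-tailed at the 5% significance level (Power=80".

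EVLW is measured at screening on Day 0 (sections 9.5.2 and 9.5.6). Randomisation is stratified by SOFA score (≤ 10, ≥ 11), and section 9.2 states: "Treatment allocation will be done using random permuted blocks within strata". No covariate of the ANCOVA is named. Sections 12 and 12.4 leave further detail to a statistical analysis plan (SAP) that is to be final before unblinding.

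**The concern.** A confirmatory claim needs one test named in advance, and it should address the hypothesis as written. This protocol offers two tests that answer different questions. ANCOVA estimates a difference in mean AUC adjusted for whatever covariates it contains. The Mann-Whitney test compares the rank distributions of unadjusted AUC and gives no difference in means. It therefore addresses neither the null hypothesis on mean AUC nor the change that the introducing sentence describes. It also has no place for Day 0 EVLW or the SOFA stratum.

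This is not a detail left open for the SAP, because the dependence on the data is a stated rule. A SAP that follows it inherits a data-dependent primary test, and one that names a single test departs from the protocol.

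At stake are which result counts as primary, how much power the trial has if the effect is smaller than planned, and whether the 5% level holds if the choice is discretionary.

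**Working it through.** **Inputs from the protocol.** 20 patients per group, two-sided 5%, 80% power, "A mean difference of at least 40% between the two application conditions", and an SD of about 40% (section 12.2). That SD is a baseline SD; using it for the AUC is an assumption.

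**Inputs assumed.** The protocol gives no correlation between Day 0 EVLW and the AUC, so 0, 0.5 and 0.7 are shown. Day 0 EVLW is taken as the only ANCOVA covariate. The SOFA stratum was not simulated.

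**The plan's own figure.** n per group = 2(1.960 + 0.842)² × (40/40)² = 15.7, so 16, or 17 with the t-test. At 20 per group, power is 88.5% (normal formula) or 86.9% (t-test). The stated inputs do not give exactly 20, but 20 is sufficient and errs on the safe side.

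**Effect read as 1.0 SD, by formula.** Baseline adjustment multiplies the SD by √(1 − ρ²). ANCOVA power at 20 per group is 88.5% at ρ = 0, 95.5% at 0.5 and 99.3% at 0.7. Mann-Whitney with relative efficiency 0.955 has an effective n of 20 × 0.955 = 19.1 and power of about 87%.

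**The same effect, simulated.**
- Normal data: ANCOVA 86%, 94% and 99% at ρ = 0, 0.5 and 0.7; Mann-Whitney about 85%.
- Skewed data (lognormal, additive shift): ANCOVA 85%, 93% and 98%; Mann-Whitney about 91%.

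**Effect read as a proportional reduction.** Lognormal AUC, CV 40%, so log-scale SD = √ln(1.16) = 0.385. A 40% reduction is then |ln 0.6|/0.385 = 1.33 log-scale SDs and a 30% reduction is 0.93, which is why these powers differ from those at 1.0 SD. Power in % (40,000 simulated trials per row):

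| Reduction | ρ | ANCOVA, log | ANCOVA, raw | Mann-Whitney | Raw − MW | Log − MW |
|---|---|---|---|---|---|---|
| 40% | 0 | 98.1 | 97.2 | 97.8 | −0.6 | 0.3 |
| 40% | 0.5 | 99.7 | 99.3 | 97.7 | 1.6 | 2.0 |
| 40% | 0.7 | 100.0 | 99.9 | 97.7 | 2.2 | 2.3 |
| 30% | 0 | 80.0 | 77.0 | 78.7 | −1.7 | 1.3 |
| 30% | 0.5 | 90.2 | 87.2 | 79.2 | 8.0 | 11.0 |
| 30% | 0.7 | 97.4 | 96.0 | 78.9 | 17.1 | 18.5 |
| 20% | 0 | 42.0 | 39.6 | 40.9 | −1.3 | 1.1 |
| 20% | 0.5 | 53.0 | 49.2 | 40.9 | 8.3 | 12.1 |
| 20% | 0.7 | 68.9 | 64.5 | 41.0 | 23.5 | 27.9 |

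**Do the two tests agree?** In these runs raw ANCOVA and Mann-Whitney differ on significance in about 2% of trials at a 40% reduction, 9% to 19% at 30% and 11% to 33% at 20%.

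**How often would the fallback be used?** Under an assumed rule (Shapiro-Wilk p < 0.05 on the ANCOVA residuals), in about 5% of trials with normal data and 37% to 60% with lognormal data.

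**Type I error.** Under that mechanical rule it is 4.8% to 5.4%. If the smaller of the two p-values could be taken, it is 6.2% at ρ = 0, 7.4% at 0.5 and 8.1% at 0.7 with lognormal data.

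**The case against.** Much can be said for the plan. At the effect for which the trial was sized, either test exceeds the planned 80% power. The loss at smaller effects depends on a correlation that the protocol does not give. At zero correlation it vanishes, and on skewed data the rank test can beat raw-scale ANCOVA. This is a 40-patient, single-centre proof-of-concept study, and its SAP may fix the criterion and covariates before unblinding. All of this stands, and it limits the size of the point.

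A reader might infer three stronger things that the documents do not support.
- That the fallback throws away covariates which the planned ANCOVA contains. The protocol names none, so the firm statement is only that Mann-Whitney cannot use Day 0 EVLW or the SOFA stratum.
- That the choice is made on unblinded results. The SAP is to be final before unblinding, and a distribution can be checked blinded.
- That the type I error is inflated. The text ties the choice to the distribution and not to the p-value, and a mechanical rule holds the level near 5%.

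What the objection does not answer is that the protocol text itself names two primary tests, one of which does not match the null hypothesis.

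**Conclusion.** The point holds as a defect of specification. Section 12.6.1 and the synopsis fix no single confirmatory test or estimate, and one of the two options tests something other than equality of mean AUC.

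The consequence for power is conditional. It is immaterial at the planned 40% effect. At a true 30% reduction it is negligible for a correlation of 0, 8 to 11 points for 0.5 and 17 to 18.5 points for 0.7. A correlation of exactly 0 is the unfavourable extreme for adjustment, since the Day 0 value is the first point of an AUC that starts on Day 0; the true value is unknown.

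The risk to the 5% level, about 6% to 8%, arises only if the more favourable test could be chosen, which the present wording does not exclude. The figures rest on 20 per group, a CV of 40% for the AUC, complete data and baseline as the sole covariate.

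**What to change.** Before unblinding, amend section 12.6.1 and the synopsis, and carry the same text into the SAP:
- Delete the clause that makes the method depend on how the data are distributed.
- Name one primary analysis: ANCOVA of EVLW AUC (Day 0 to Day 7) on treatment, Day 0 EVLW and SOFA stratum (≤ 10, ≥ 11), two-sided 5%, reported with its 95% confidence interval.
- Fix the scale, raw or log, in advance. If log is chosen, restate the hypothesis as a ratio of geometric means, because the null now refers to arithmetic means.
- Keep a rank test, preferably stratified by SOFA, as a sensitivity analysis only.

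The cost is wording; both covariates are already collected. Two covariates use two degrees of freedom (error degrees of freedom 40 − 4 = 36, against 40 − 2 = 38 without them), or one if baseline was intended anyway. On the log scale some power would be lost if AUC is truly normal.
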